### Data collection, management, and monitoring

The data will be collected through paper-based documents written by the clinical research coordinator and outcome assessors. All original data sources will be stored in limited-access areas for 3 years. A clinical research associate independent from the funder and competing interests will monitor the clinical trial during the study period. The clinical research associate will monitor the written informed consent documents, recruitment status, protocol compliance, overall trial progress, data quality, timelines of data collection, treatment administration, and other relevant trial aspects and processes. The Ministry of Food and Drug Safety (MFDS) in Korea will carry out audits at regular intervals.

## Discussion

A systematic review of acupuncture for treating sciatica found that the use of acupuncture may be more effective than drugs and may enhance the effect of drugs for patients with sciatica, but because of the insufficient number of relevant and rigorous studies, the evidence is limited [20]. Among the included 11 studies, six used EA, two used manual acupuncture, and three used warming acupuncture as intervention. We adopted a complex intervention of manual acupuncture plus EA treatment because it is the most common approach used by DKMs in South Korea today.

Recently, neurophysiological studies for chronic pain are increasing [15–19] because emotional state, perception, modulation, and chronification all play an extremely important role in chronic pain [28, 29]. Kaneko et al. [59] demonstrated that the presence of psychiatric problems was associated with attenuated activity of the nucleus accumbens (NAc) in chronic LBP and dysfunction of the NAc might potentially be involved in the affective/motivational factors in the chronification of LBP. Thus, we designed a study protocol to examine the effect of acupuncture on parameters of emotion and coping strategy with neuroimaging as well as bothersomeness and pain intensity in patients with chronic sciatica.

In the fMRI scanning session, both TASK 1 and 2 were designed to investigate the interaction between negative and neutral emotional states and experimental bothersomeness in the essential pain-processing network [60]. As we decided to use the VAS for bothersomeness as the primary outcome measurement other than the VAS for pain intensity to understand the impact of chronic pain on patients in this study, we adopted this bothersomeness and emotion stimuli model scan run using the StiMus® MRI-compatible surface electrode to induce experimental bothersome stimuli other than pain stimuli. In TASK 3, we selected the LBE pain model because it is intuitive and has a simple methodology, induces a similar pain sensation to clinical pain in patients, and is a MRI-compatible pain model for neuroimaging study [61, 62]. The fMRI data analysis will be conducted to compare not only the acupuncture group with sham control group but will also compare responders with non-responders.

We chose non-penetrating sham acupuncture plus placebo acupuncture without electrical stimulation at non-traditional acupuncture points for the control group. Park et al. validated the complete subject blinding of sham acupuncture as the control group [38], and we will evaluate the blinding index [33] of the acupuncture and sham acupuncture treatments after the first acupuncture treatment and at endpoint. For valid blinding of placebo EA, the ES-160 dummy device was designed to have no electrical stimulation by insulating electrodes, similar to a previous study [63]. The intensity of electrical stimulation from both real and sham devices will be maintained under a certain level so that subjects in either group cannot perceive the electric current. Patients will be informed about the two types of acupuncture in the study as follows: “In this study, different types of acupuncture will be compared. The electric current will flow but with intensity under a fixed level which you cannot detect.”

This randomized, patient-assessor blind, sham-controlled clinical trial should provide important evidence for the efficacy of acupuncture for chronic sciatica and will help improve our understanding of the neurophysiological mechanism of acupuncture on the interaction between emotional state and chronic pain. The Standard Protocol Items: Recommendations for Interventional Trials (SPIRIT) Checklist for this protocol is attached in Additional file 2.

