### Study design

This clinical research protocol is designed to assess the effect and mechanism of acupuncture for chronic sciatica on pain and associated emotional disorder and will be processed with a randomized, two-arm, parallel, patient-assessor blinded, and non-penetrating sham-acupuncture controlled study. The trial will be performed in the Korean Medicine Hospital of Kyung Hee University at Gangdong in Korea. All participants will be enrolled through voluntary participation and written informed consent will be obtained in accordance with the Declaration of Helsinki and the Guidelines for Good Clinical Practice. Interventions for a given trial participant may be discontinued at any time during the trial based on participant request to discontinue or in cases of significant clinical worsening as judged by Doctors of Korean Medicine (DKMs). This protocol is registered with the U.S. National Institutes of Health Clinical Trials registry (NCT03350789). Eligible participants will be randomly allocated into one of two groups at a 1:1 allocation ratio, blinded to the group allocation, and receive treatment for 4 weeks. The experimental group will undergo real acupuncture treatment (verum manual acupuncture plus electroacupuncture (EA)) and the control group will undergo sham acupuncture treatment (acupuncture without skin penetration plus EA without electrical stimulation) twice a week. The effect on parameters related to bothersomeness, pain, and emotional disorder will be assessed at baseline and endpoint. The fMRI scanning will be conducted for 52 subjects (20 among the 34 experimental subjects, 20 among the 34 sham control subjects, and an additional 12 normal control subjects without any intervention; the normal control group of 12 subjects is for the analysis of fMRI data, not for the main analysis of the primary outcome, the VAS for bothersomeness as they do not have chronic sciatica and do not receive any interventions. They just serve as the normal control with fMRI scans performed twice) at baseline and endpoint. Outcome assessment and statistical analyses will be performed by professionals blinded to the assignment of participants to either the real or sham acupuncture groups. The study flow chart is presented in Fig. 1 and the trial timetable is depicted in Fig. 2.

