### Outcome

#### Primary outcome measurement

The primary outcome measure is the bothersomeness of chronic sciatica as assessed by VAS [43]. To understand the impact of chronic sciatica on the patients, we decided to use the VAS for bothersomeness as the primary outcome measurement other than the VAS for pain intensity. Bothersomeness will be quantified using the VAS score as determined on a 100-mm horizontal line (0, no bothersomeness; 100, intolerable bothersomeness). Participants will be asked to mark the degree of bothersomeness due to sciatica experienced during the previous week at baseline (visit 2), before each treatment session (visits 2–9), and at each post-treatment follow-up visit (visits 10–11); the primary endpoint will be VAS for bothersomeness score at visit 10, i.e., 1 week after completion of the eight sessions of acupuncture treatment. The outcome measures will be assessed before treatment at each visit.

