### Sample size

Referring to a previous study [52], an appropriately powered full-scale sample size was estimated using the mean difference of VAS for bothersomeness due to sciatica between groups in the primary endpoint. The researchers expect the mean difference will be 12.4 mm with a standard deviation (SD) of 16.2 mm between the two groups, which is not moderately clinically meaningful but represents a minimally important difference [53].

Considering the mean comparison method of the two-sample *t* test model with a two-tailed test, 80% test power, and a 5% significance level, the total number of individuals required per group is 27. For equal allocation of the two groups, the total sample size required when considering a dropout rate of 20% is 68 subjects with 34 subjects in each group.

Considering the nature of fMRI studies that use approximately 90,000 voxels to estimate the BOLD signal indirectly and for which conventional power calculations are meaningless, we determined 20 subjects in each group for fMRI scanning according to the trend of related neuroimaging studies [54–58]. Most studies decided that 20 participants is an adequate sample size regarding the high cost of fMRI examinations.

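### The planned fMRI comparison of responders with non-responders splits 40 scanned patients after treatment: it loses at least about 36% of the information if a continuous score is cut and, if the arms are pooled, partly measures treatment arm

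*Protocol article*

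**What the plan says.** The Discussion of the protocol article commits the fMRI analysis to two contrasts: it will set acupuncture against sham, "but will also compare responders with non-responders". Study design gives the scanned patients as "20 among the 34 experimental subjects, 20 among the 34 sham control subjects". A further 12 normal controls are scanned, but they have no sciatica and cannot be responders. Sample size sets the number by precedent rather than by a power calculation ("we determined 20 subjects in each group for fMRI scanning").

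The article does not define a responder, give a cut-off, or say whether the second contrast is pooled over arms, made within arms or adjusted for arm. The fMRI part of Statistical analysis describes GLM and independent component analysis and does not mention responders. The primary clinical measure is continuous, on a 100-mm line: "the primary endpoint will be VAS for bothersomeness score at visit 10".

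**The concern.** The responder contrast is the only analysis in the article that ties imaging to clinical outcome patient by patient, so a mechanism claim could lean on it. It has three weaknesses.

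- **Not randomised.** Response is observed after treatment. The contrast stands beside the randomised one without that caution.
- **Information lost.** Cutting a continuous score into two groups treats a patient just over the cut like one far over it. With 40 patients and no power calculation, no planned margin absorbs the loss.
- **Possible mixing with arm.** If acupuncture works, more responders come from the acupuncture arm. The arms also differ in skin penetration, electrical stimulation and point location, any of which might change the brain signal without relieving symptoms. A pooled, unadjusted contrast could pick up such a change and present it as a correlate of relief.

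**Working it through.** **Inputs from the protocol article.** Planned effect and spread: "the mean difference will be 12.4 mm with a standard deviation (SD) of 16.2 mm" (Sample size). Test: "with a two-tailed test, 80% test power, and a 5% significance level" (Sample size). Allocation: "randomly allocated into one of two groups at a 1:1 allocation ratio" (Study design). Scanned patients: 20 + 20 = 40 (Study design).

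**Assumptions, not in the article.** Response is taken from VAS bothersomeness; the score is normal; the planned effect is true. For the arm-mixing steps only: arms are pooled without adjustment.

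**1. The plan's own figure.** n per group = 2(1.96 + 0.84)² × 16.2² / 12.4² ≈ 26.8, so 27. Dropout: 27 / 0.8 = 33.75, so 34 per group and 68 in total. Both reproduce. (With the exact t test, 27 per group gives 78.8% power and 28 gives 80.3%, a trivial difference.) The article gives no such figure for the responder contrast. The standardised effect is d = 12.4 / 16.2 = 0.765.

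**2. Information kept after a split.** If a fraction p lies above the cut c, the efficiency relative to the continuous score is φ(c)² / [p(1 − p)].

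| Split | Kept | Lost | 40 patients act like |
|---|---|---|---|
| 50/50 | 2/π = 63.7% | 36.3% | 25.5 |
| 40/60 | 62.2% | 37.8% | 24.9 |
| 30/70 | 57.6% | 42.4% | 23.0 |
| 20/80 | 49.0% | 51.0% | 19.6 |

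The median split is the best case. This step does not depend on pooling.

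**3. What that does to power.** By Fisher's z with n = 40, an assumed brain-response correlation of 0.43 gives 79.9% power with the continuous score. It gives 58.5% after a median split, 54.0% at 30/70 and 47.2% at 20/80.

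**4. Arm mix, if pooled.** Take two normals 0.765 SD apart with a common cut. At 50% overall response the cut lies midway: Φ(0.765 / 2) = 64.9% of acupuncture and 35.1% of sham patients respond, about 13 and 7 of 20. With equal arms, the acupuncture share is 64.9% among responders and 35.1% among non-responders. The part of any arm effect that enters the contrast is 0.649 − 0.351 = 0.298. At 30% overall response the shares are 71.3% and 40.9%, a difference of 0.304. The leak is about 30% either way.

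**5. False signals, if pooled.** Simulation: 20,000 runs, 20 + 20 patients, pooled median split, a brain effect that depends on arm only and is unrelated to response within arm.

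| Arm-only brain effect (SD) | Pooled contrast rejects | Responder status with arm in the model rejects |
|---|---|---|
| 0 | 4.8% | 4.9% |
| 0.5 | 7.3% | 4.9% |
| 0.8 | 10.8% | 4.9% |
| 1.0 | 13.5% | 5.0% |
| 1.5 | 21.0% | 5.0% |

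Adding arm removes the inflation. It does not recover the information lost in step 2.

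**The case against.** The strongest reply is that the article never says the contrast is pooled or unadjusted. It is one clause in a Discussion. The responder definition, the cut-off and the group-level covariates may stand in a fuller protocol or analysis plan that is not shown, and their absence is not an error. A within-arm or arm-adjusted contrast fits the sentence too. This stands, and the mixing result is therefore conditional. A reader might infer that the plan certainly confounds response with arm; the text does not support that.

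It is also true that the article does not tie response to VAS bothersomeness or to a median split. The loss of about a third is the best case of an assumed cut, not a property of the plan.

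A reader might further infer that a brain effect of needling itself would be reported as the neural basis of relief. The simulation does not bear that out: even at 1.5 SD, the pooled contrast misses such an effect about four times in five. It could be so reported, more often than the nominal 5%.

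Finally, continuous change is also a post-treatment variable, and a regression on it is no more randomised than a responder contrast. That stands as well. The gain from the regression is in information and in control for arm, not in causal status.

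None of this answers the central point: a two-group responder contrast is planned, and if a continuous score is what is cut, information is lost whether or not the arms are pooled. A within-arm contrast avoids mixing but leaves about 10 against 10 patients in an arm at 50% response, or 13 against 7 under the planned effect.

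**Conclusion.** The point holds in a limited form. The plan states a contrast between groups formed after treatment in 40 scanned patients. If a continuous, roughly normal score is cut, at least about 36% of its information goes, rising to about 51% at a 20/80 split. If arms are also pooled without adjustment, about 30% of any arm effect enters the contrast, and the error rate for an effect due to arm alone rises from 5% to between 7% and 21% over the range examined. That second part assumes the planned effect is true and that the planning SD applies to the score that defines response.

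Severity is low to moderate. The contrast supplements the randomised imaging comparison, which is kept, and the primary outcome and sample size are untouched.

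**What to change.** Make the brain-response analysis a regression of the change in each imaging measure on the continuous change in VAS bothersomeness (visit 10 minus visit 2), with arm as a covariate. An arm-by-change term may be added as exploratory, since it is imprecise with 20 patients per arm. Report any responder/non-responder contrast only within arm or adjusted for arm, with its cut-off fixed before the data are seen, and label it exploratory and non-randomised.

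The cost is a changed group-level model and a few sentences of text, with no new data or scans. A slope is harder to picture than two groups, and the association remains observational, so the text should claim no more than that.

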#### Acupuncture treatment group

The acupuncture group will receive manual acupuncture plus EA treatment at the same time twice a week for 4 weeks, which is the common approach used by DKMs in South Korea today. The predefined acupuncture points will be carefully selected by a process of consensus with participating DKMs who all specialize in Rehabilitation Medicine of Korean Medicine on the basis of a literature review regarding acupuncture for LBP and sciatica. The seven essential acupuncture points selected are as follows: unilateral (the affected side) *Huantiao* (GB30) for manual acupuncture and *Jiaji* (EX-B2) points at L4 and L5, *Shenshu* (BL23), *Dachangshu* (BL25), *Weizhong* (BL40), and *Yanglingquan* (GB34) for EA. To make the acupuncture treatment reflect an ordinary clinical practice condition, additional individualized manual acupuncture points of 8 or less (a total of 15 or less acupuncture points with the seven essential points) will be chosen by the practitioners among the predefined group of optional acupuncture points categorized according to the three types of meridian patterns identification (Gallbladder meridian pattern, Bladder meridian pattern, and Mixed pattern) [36].

Manual acupuncture treatment will be administered using disposable sterile stainless-steel needles (40 mm × 0.25 mm; Dong-bang Acupuncture Inc., Seoul, Korea) to the acupuncture points mentioned above with the aid of the tube of sham acupuncture needle device. The needles will be inserted perpendicular to a depth of 5–20 mm with the patient lying face down after skin sterilization, followed by bidirectional rotation to induce *Deqi* sensation and left in place for 15 min.

At the same time, the six needles inserted to the predefined EA points will be connected to the ES-160 electrical stimulator. Electrical stimulation will consist of a biphasic waveform current, which utilizes alternating interrupted waves and continuous waves at 50 Hz in a triangular form and a compressional wave [37] for 15 min.

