#### Sham acupuncture control group

The sham acupuncture group will receive non-penetrating sham acupuncture as control for manual acupuncture plus placebo acupuncture without electrical stimulation as the control for EA at the same time twice a week for 4 weeks.

Sham acupuncture treatment will be administered using non-penetrating disposable sterile stainless-steel sham needles (40 mm × 0.25 mm) as described by Park et al. (AcuPrime Co., Ltd., Exeter, UK) [38] to a total of 15 or less predefined non-traditional acupuncture points: 2 cm lateral to the each acupuncture point of the acupuncture group. Except for the use of a semi-blunted needle, the technique will be the same as performed in the acupuncture group.

At the same time, the six sham needles inserted to the predefined non-traditional EA points (2 cm lateral to each EA point of the real acupuncture group) will be connected to the ES-160 dummy device that is designed to have no electrical stimulation through insulation of electrodes and be left in place for 15 min.

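### The patient script says that current will flow, but the protocol gives the sham arm no current, and one Discussion sentence ascribes a stimulation intensity to both devices

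*Protocol article*

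**What the plan says.** The Acupuncture treatment group section describes the active electrical component by waveform, frequency and a duration of 15 min: "Electrical stimulation will consist of a biphasic waveform current, which utilizes alternating interrupted waves and continuous waves at 50 Hz in a triangular form". It gives no intensity there.

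The Sham acupuncture control group section connects the sham needles to a "dummy device that is designed to have no electrical stimulation through insulation of electrodes". The Abstract and the Study design section also describe the sham electroacupuncture as being without electrical stimulation.

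The Discussion returns to the subject in three steps. It first repeats that "the ES-160 dummy device was designed to have no electrical stimulation by insulating electrodes". It then says that stimulation from both real and sham devices will be "maintained under a certain level so that subjects in either group cannot perceive the electric current". Finally it quotes the information for patients, which says that different types of acupuncture will be compared and adds: "The electric current will flow but with intensity under a fixed level which you cannot detect". Nothing in the text restricts that script to one arm.

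**The concern.** Two things do not fit together. First, a device whose electrodes are insulated so that it gives nothing has no intensity to keep under a level, yet the Discussion ascribes one to it. A reader cannot tell whether the limit is a rule for the real device only, a rule for how both devices are operated, or a sign that the dummy delivers something.

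Second, and more firmly, the script makes a factual statement to all patients that the protocol itself contradicts for the sham arm. The Study design section commits the trial to written informed consent in accordance with the Declaration of Helsinki. Not telling patients which arm they are in is ordinary blinding. Telling them that a current will flow when the design ensures that none does is a different matter, and it is avoidable.

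A smaller matter follows. If the imperceptibility limit is the operating rule, it defines part of the intervention, but it appears only in the Discussion and not where the intervention is described.

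**Working it through.** No formula decides this point. The check is whether the statements can all be true together.

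1. **Sham output.** Four places give none: the Abstract, Study design, Sham acupuncture control group and the Discussion. The last two attribute it to insulated electrodes.
2. **Active output.** The Acupuncture treatment group section specifies a 50 Hz biphasic current for 15 min, so the real device delivers current.
3. **The limit.** For the real device, keeping current below perception is a meaningful restriction. For an insulated dummy there is nothing to restrict, and zero output meets the limit automatically. Items 1 and 3 are therefore compatible in effect, but not in wording, because the limit is phrased as applying to stimulation from both devices.
4. **The script.** It makes two assertions, which can be tested by arm:
   - *Current flows.* Active arm: true. Sham arm: false, by item 1.
   - *The patient cannot detect it.* Active arm: true if the limit works. Sham arm: true, because there is nothing to detect.

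   Only the second assertion can hold in both arms.
5. **How many are affected.** Allocation is 1:1 with 68 patients, so 68 / 2 = 34 sham patients, or 34 / 68 = 50% of those randomized.
6. **Planned numbers.** From the Sample size section (difference 12.4 mm, SD 16.2 mm, two-sided 5%, power 80%), the normal approximation gives 2 × (1.960 + 0.842)² × (16.2 / 12.4)² = 26.8, so 27 per group. With 20% dropout, 27 / 0.8 = 33.75, so 34 per group and 68 in total. The stated figures reproduce, and none of them depends on the script or on the device output.

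**The case against.** The strongest reply is that the Discussion sentence is loose writing. Zero output is imperceptible too, the sentence just before says that the dummy gives no stimulation, and few readers would conclude that sham patients receive current. That is largely right for the sentence about the devices. It does not rescue the script, which addresses the patient directly and says that current flows.

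A second reply is that the article condenses a longer protocol. The Intervention section refers to Additional file 1 for detailed procedures, and that file may state an intensity. This stands: the lack of a numerical setting in the article is not a finding. But no such file can make the quoted sentence true for a patient on an insulated device. It also stands that only two sentences of patient information are visible, so nothing can be said about the rest of the consent material.

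A reader might go on to three stronger conclusions, which the article does not support.

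- **That an imperceptible current conflicts with the claim to reflect ordinary practice.** The phrase "To make the acupuncture treatment reflect an ordinary clinical practice condition" opens a sentence about optional manual points. The statements about the common approach concern combining manual acupuncture with electroacupuncture and, in the intervention section, its schedule. Nowhere does the article say what intensity is usual or that it is usually felt.
- **That one fixed level must fail for some patients.** The word fixed occurs only in the lay script. The operational sentence defines the limit by its result, which is compatible with setting it individually.
- **That the primary comparison is biased by a calculable amount.** The article gives neither a probability that an active patient feels current nor an effect of doing so on the bothersomeness rating, and any figure would also depend on whether such events recur in the same patients. Checks already exist: needle sensation and the blinding index after the first treatment (Randomization section), and the blinding index again at endpoint (Discussion).

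**Conclusion.** The point holds as a defect of wording with a consequence for participants. On the protocol's own description of the dummy device, the quoted statement is untrue for the 34 patients planned for the sham arm. The sentence giving both devices a stimulation intensity is at odds with the statement immediately before it.

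This rests on two assumptions: that the dummy performs as the protocol says, and that the script is read to all patients as quoted. If either is wrong, the text still needs correcting, because the sections would then misdescribe the device or the information given.

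There is no statistical size to report. The sample size, primary endpoint and analyses are unaffected, and the documents do not show that the trial tests something other than usual practice or that its result will be biased.

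**What to change.** 1. Reconcile the Acupuncture treatment group section, the Sham acupuncture control group section and the Discussion so that they say the same thing about what each device delivers and to which device the imperceptibility limit applies. This review proposes no intensity.
2. Replace the script sentence with neutral wording that is true in both arms and gives no help in guessing the arm, for example that patients are not expected to feel any current from the device. Use it for patients enrolled from then on, subject to IRB review.
3. If the limit stands after reconciliation, say in the intervention description and in the trial's conclusion that the electrical component tested was kept below perception.

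Do not add a question at every session on whether current was felt, or a sensitivity analysis built on the answers. The question could prompt patients to guess their arm, and felt current is a post-randomization event that can truly arise only in the active arm, so conditioning on it would undo the randomized comparison. The planned blinding index already serves to detect unblinding.

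The cost is small: a text amendment and an IRB submission. Recruitment began in March 2018, so patients enrolled before and after the change would have heard different wording, and expectancy may shift slightly, in both arms alike.
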